### Variables and instruments

The study variables are organized into eight groups: i) Nutritional status; ii) Dysphagia; iii) Food quality and environment; iv) Socio-demographic variables; v) Clinical, functional, cognitive, and frailty variables; vi) Variables related to the risk profile; vii) Context variables; viii) Variables related to the care process.

Specifically, nutritional status and dysphagia are considered the main variables of the study. Likewise, the variables related to nutritional status are organized into:

Risk of malnutrition on admission: Malnutrition Universal Screening Tool (MUST) will be used to determine the risk of malnutrition. This questionnaire will measure current weight (kg), estimated weight three months ago (kg), height (cm), and Body Mass Index (BMI) (kg/m2). If height and weight cannot be measured or obtained, they will be estimated mid-upper arm circumference (MUAC) and calf circumference (CC) are set for weight and forearm length for height by the nutrition staff of each hospital. All patients included in the study will be assessed on admission, every 7 days, and at discharge.Diagnosis of malnutrition and degree of severity at admission: Global Leadership Initiative on Malnutrition (GLIM) criteria will be used for the population identified as high risk according to MUST. In addition, the following biochemical parameters will be collected: albumin, prealbumin CRP, CRP/prealbumin ratio, transferrin, total cholesterol, and the total number of lymphocytes. They will be collected on admission, every 7 days, and discharge provided that the minimum time for their re-determination has elapsed.Type of nutritional care established (according to risk and diagnosis of malnutrition): Includes aspects such as referral to the nutrition and dietetics unit, dietary adaptation according to alteration, nutritional supplementation, type of nutrition, or nutritional education. It will be recorded within 48 hours of admission, every 7 days and at discharge, and in case of any modification in the selected intervention, the starting date should be noted.Daily intake: a semi-quantitative questionnaire will be used to record the amount of intake made during the days of admission.

The variables related to dysphagia include the determination of suspected dysphagia with the EAT-10 questionnaire. In the case of suspicion, a clinical examination will be carried out to diagnose dysphagia and classification with the MECV-V questionnaire [24]. Likewise, the type of care received will be recorded according to the presence and type of dysphagia. Both instruments will be used at admission and discharge of all patients included in the study. Patients with a prolonged stay will be re-evaluated every 7 days.

In addition, the study includes a wide variety of variables related to the care process, functional status, cognitive status and comorbidities, frailty, dietary quality, and context variables. Likewise, multiple instruments will be used depending on the type of variable and other complementary instruments will be used to collect the most relevant socio-demographic and clinical data.

### Data collection

In each participating hospital, there will be a site manager and a research team consisting of nurses, nutritionists, doctors, speech therapists, endocrinologists, and technical staff. The principal investigator of the project ([name]) will coordinate the centre managers. Each figure will be assigned specific roles related to data security and ethical issues. In particular, the site managers will be responsible for the coordination and supervision of the recruitment process and data collection in their respective hospitals. Data collection will be adapted to the specificities and material and human resources of each of the centres collaborating on the project. Fig 1 shows a flow chart of how the process of recruiting participants will be carried out, as agreed by all the participating centres.

**Fig 1 pone.0288348.g001:**
[figure not shown]
Flowchart of the recruitment of participants.

In each centre, a researcher will undertake the daily recruitment of participants by reviewing the hospital admission register and electronic medical records to verify compliance with the selection criteria. If the patient meets the selection criteria, this investigator will locate the patient’s admission unit, inform the patient personally and in detail about the study (delivery of the study information sheet) and invite the patient to participate, obtaining written informed consent. He/she will then inform the data collection coordinator and the centre manager.

The data collection process will be grouped into three phases (Fig 2).

**Fig 2 pone.0288348.g002:**
[figure not shown]
Flowchart of the data collection.

#### Phase 1: Baseline situation

At the beginning of data collection, the facility manager will be responsible for recording the characteristics of the hospital nutrition unit and the hospital food service.

In the first 24–48 hours of admission, the nursing and nutrition staff will start collecting data related to functional variables (Barthel Index), clinical variables (diagnosis; renal or liver disease), cognitive variables (Pfeiffer questionnaire), frailty (polymedication; Frail questionnaire; Charlson index), risk profile (Braden scale; active infection), socio-demographic (Gijón scale), hospitalization and context (hospital; hospitalization unit), anthropometric parameters (height; weight; BMI), dysphagia-related variables (EAT-10; MECV-V) and malnutrition (biochemical profile; MUST; GLIM criteria).

Specifically, if the patient obtains a result ≥ 2 in the MUST questionnaire, the GLIM criteria will be applied by the nutritionists/endocrinologists to stratify the severity of malnutrition and the type of nutritional care will be adapted. On the other hand, if the patient obtains a result ≥ 3 in the EAT-10 questionnaire, an enter consultation with a speech therapist and endocrinologist or nutritionist will be requested for an in-depth assessment of the dysphagia with the MECV-V questionnaire and to adapt the nutritional care. In addition, the team of nutritionists at each centre will provide and explain to the patient or their companion the daily intake record booklet, which the patient or guardian must fill in during their hospital stay and which will be supervised in the morning shift by the nurse or nutritionists participating in the study. Similarly, within the first 24 hours of admission, the person responsible for the study in each hospital will contact the medical team to add the biochemical profiles (albumin, pre-albumin CRP, CRP/prealbumin ratio, transferrin, total cholesterol, and the total number of lymphocytes).

#### Phase 2: Follow-up

Participants will be monitored every 7 days until they are discharged from the hospital. In this way, the researchers in charge will make a forecast of follow-up dates. In addition to the variables indicated, the nutritional care established will be adapted according to the evolution of the nutritional status and degree of dysphagia of the patient during their hospital stay, as part of the usual practice in each centre. On each occasion, a record will be kept of the person collecting the data.

#### Phase 3: Situation on discharge

In addition to the variables indicated, on the day of discharge from the hospital, the daily intake record book will be collected and the food satisfaction survey will be provided. The variables related to the care process (days of stay, hospital mortality, and whether it was early readmission) will also be recorded.

Finally, the patient will be given the continuity of care report at discharge, drawn up by the responsible physician together with the nursing recommendations and information sheets on care related to malnutrition or dysphagia, as appropriate.

Data collection will be carried out electronically through Research Electronic Data Capture (REDCap) (www.prooject-redcap.org) [25,26]. This is a web application that allows the creation of electronic data notebooks for research projects and their online and offline collection from computers and other mobile devices. It also includes a scheduling and alarm system to manage data collection during monitoring. In this regard, it should be noted that the researchers who take on the data collection will receive training on the operation of REDCap and that a pilot of the process of recruiting participants and data collection will be carried out for one month.

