## Materials and methods

### Research hypothesis

The nutritional status of patients aged 65 years and over admitted to the medical and surgical inpatient units of the participating hospitals evolves unfavourably from admission to discharge and may increase the length of stay, hospital mortality, and early readmission.

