### Aims

The main objective of this project is to assess the risk of malnutrition and nutritional status on admission and its evolution until discharge, in patients aged 65 and over admitted to medical and surgical units in hospitals of the Spanish National Health System. In addition, the aim is to respond to the following specific objectives:

To identify the incidence and prevalence of risk of malnutrition and the presence of malnutrition and associated factors on patient admission and discharge.To describe the evolution of nutritional status during patient hospitalization.To analyze the average length of stay, hospital mortality, and early readmission as a function of nutritional status at admission and the presence of dysphagia in the study cohort.To determine the incidence and prevalence of dysphagia and associated factors on admission and discharge.To determine satisfaction with the quality of patient nutrition at discharge, the type of hospital food service, and the characteristics of the hospital nutrition unit.

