### Data analysis

A descriptive analysis of all the study variables will be carried out, using the appropriate measures according to the type of variable and their corresponding 95% CIs. Firstly, depending on the groups to be compared and compliance with the application requirements, a bivariate analysis will be performed, including the chi-squared or Fisher’s exact test (qualitative variables) and Student’s t-test, ANOVA, Mann-Whitney U-test, or Kruskal-Wallis (quantitative variables), depending on the application conditions.

For the analysis of the evolution of the risk of malnutrition, McNemar’s test or Cochran’s Q test will be used for qualitative variables and paired t-test or Friedman’s rank test for quantitative variables. The incidence of risk of malnutrition and undernutrition will be calculated, as for dysphagia, during the care process and at patient discharge, estimating their corresponding Odds Ratios and 95% CI using logistic regression models.

To assess the possible risk factors for both malnutrition and dysphagia and the socio-demographic and clinical characteristics of the patients, multivariate logistic regression models will be constructed. As independent variables will include: type of nutritional care established according to the risk of malnutrition; daily intake; suspected and diagnosed dysphagia and days of stay. As control variables will include: those related to the risk profile; sociodemographic (sex, age); clinical, functional, cognitive and frailty variables. In the case of mortality and time to readmission, multivariate Cox regression models will be fitted. Independent variables will be included: level of risk of malnutrition at admission; diagnosis of malnutrition at admission; change in risk of malnutrition at admission, at 7 days and at discharge; change in nutritional status at admission, at 7 days and at discharge. Control variables will include: type of nutritional care established (according to risk of malnutrition); daily intake; contextual; related to risk profile; sociodemographic; clinical, functional, cognitive and frailty variables; suspected and diagnosed dysphagia. In all multivariate models, possible interaction effects and possible collinearity will be analyzed.

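### Readmission is collected only as an undated yes/no item in the discharge phase, which does not fit the objective or the Cox model for time to readmission

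*Protocol article*

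**What the plan says.** **As an outcome.** The Research hypothesis states that nutritional status "evolves unfavourably from admission to discharge and may increase the length of stay, hospital mortality, and early readmission". The third specific objective under Aims is "To analyze the average length of stay, hospital mortality, and early readmission as a function of nutritional status at admission" and the presence of dysphagia. The Discussion part of the abstract and the Conclusions both promise results on early readmission.

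**As an analysis.** Data analysis states: "In the case of mortality and time to readmission, multivariate Cox regression models will be fitted". The predictors listed for these models include "change in nutritional status at admission, at 7 days and at discharge".

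**As collected data.** Under Data collection, "The data collection process will be grouped into three phases": baseline, follow-up and discharge. Phase 2 says: "Participants will be monitored every 7 days until they are discharged from the hospital". Phase 3 first says that "on the day of discharge from the hospital, the daily intake record book will be collected and the food satisfaction survey will be provided", and its next sentence reads: "The variables related to the care process (days of stay, hospital mortality, and whether it was early readmission) will also be recorded". Within the description of data collection, this is the only mention of readmission.

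**The concern.** The outcome and analysis sections need an event that happens after the patient leaves hospital, with a date. The data-collection sections describe observation up to discharge and an item that says whether, not when.

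If sites follow the text as written, the form can be filled in completely and still hold nothing from which a time to readmission can be calculated.

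The wording adds a second risk. The item sits beside days of stay and hospital mortality, which both describe the index admission, so staff may take it to ask whether the present stay is a readmission. If the answer were then analysed as the outcome, nutritional status at admission, and its change up to discharge, would be related to something already settled when the patient arrived.

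**Working it through.** There is no figure to recompute for this point, so the check compares what the model needs with what the article says is recorded.

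1. **Start of the risk period.** The hypothesis concerns decline between admission and discharge, and the Cox predictors include changes measured at discharge. Patients cannot be at risk of readmission before they are discharged, and these predictors are not complete until then. The clock therefore starts at live discharge.

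2. **End of the described observation.** Phase 2 monitoring runs to discharge. Phase 3 is the discharge situation, and no fourth phase is described. The article's 18 months for recruitment and follow-up is a study-level duration and gives no period after discharge for the individual patient. The described observation thus stops where the risk period starts, and the described time at risk is 0 days.

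3. **What a Cox model needs against what is recorded.**

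| Needed for time to readmission | Stated in the article |
|---|---|
| Time origin | Discharge, by implication from the predictors |
| Event indicator | A yes/no item in Phase 3, open to two readings |
| Event date | None stated |
| Window that defines early | None stated |
| Censoring date | None stated |
| Source of information after discharge | None stated for readmission |

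4. **Both readings of the item.**
   - *Index-stay reading* (was this admission itself an early readmission?): the item can be answered at discharge, but it describes an event before the exposure. It may serve as a covariate, not as the outcome.
   - *Outcome reading* (was the patient readmitted early afterwards?): the time order is right, but the answer cannot be known on the day of discharge. If it is filled in later, it is still a yes/no answer without a time.

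   Neither reading gives the data for the stated model.

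5. **Could the missing-data plan cover this?** The article proposes multiple imputation for losses to follow-up. Imputation needs some patients with the outcome observed, and the described collection yields no readmission times from which to build the imputation model.

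6. **Sample size, for completeness.** The stated size reproduces: 1.96² × 0.5 × 0.5 / 0.05² = 384.15, rounded up to 385; 385 / (1 − 0.15) = 452.9, rounded up to 453; 9 × 453 = 4077. It rests on the precision of a prevalence and not on readmission events, so this point does not alter it.

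**The case against.** The case on the other side has real force in four places.

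- **The timing is partly inferred.** The words fixing the day of discharge belong to the sentence about the intake booklet and the survey. The sentence on care-process variables carries no date of its own and is tied to discharge by its section heading and its neighbour. This stands.
- **The index-stay reading is only one reading.** Every other section treats readmission as an outcome, so the phrase may simply be loosely worded. This stands too, and the consequence of an event preceding the exposure must stay conditional on that reading.
- **Records could supply the dates.** A researcher at each centre already reviews the admission register and electronic records daily for recruitment, and the limitations section shows that electronic records are also a source of study data. A limit on patient monitoring is not a limit on record extraction. This is fair, but nowhere does the text say that readmissions will be extracted in this way.
- **The detail may lie elsewhere.** The data-collection flowchart (Fig 2) is not shown, and an article condenses a fuller protocol. The definition of early and the censoring date could be given there.

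These objections rule out a stronger conclusion that a reader might draw: that the study will certainly have no readmission data, that every readmission will go unobserved, or that the analysis does reverse time order. The documents do not support such absolute statements.

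They do not remove the conflict. The article is not merely silent: it fixes the form of the item, the phase in which it is recorded and the end of monitoring, and these do not fit the model it also fixes. Even the most favourable reading leaves an undated yes/no flag.

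**Conclusion.** The point holds as a conflict between the described data collection and the stated analysis. As written, the article provides no event or censoring times for the time-to-readmission model, and its single readmission item is ambiguous about which admission it describes.

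The size is limited. Readmission is one of three outcomes in one of five specific objectives. The main objective, length of stay, hospital mortality (which can be known at discharge) and the sample size are untouched. A reader might attach a scale of 4077 × 0.85 = 3465 patients to the problem, but the 15% loss allowance belongs to the prevalence calculation and says nothing about readmission.

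The conclusion assumes that the Phase 3 item belongs to the discharge assessment, as its heading indicates, and that neither Fig 2 nor the full protocol adds a readmission check after discharge. If either does, the article's text still has to be brought into line with it.

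**What to change.** Reconcile Phases 2 and 3 of Data collection with Data analysis:

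1. Add a dated look-up of first readmission, and of death, from the hospital admission register and electronic records, at a fixed time after discharge. The sponsor should state the window that it defines as early.
2. Start the clock at live discharge, so that in-hospital deaths do not enter the risk set, and state the censoring date. The date of death is needed because death ends the time at risk of readmission; how the model handles it can be left to the analysis plan.
3. Record separately, with unambiguous wording, whether the index stay was itself a readmission, and use that item only as a baseline covariate.
4. If the look-up is not feasible, remove readmission from the hypothesis, specific objective 3 and the Cox analysis, and from the results promised in the abstract and Conclusions.

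The cost is small: one passive record check per discharged patient using sources that the sites already consult, one further REDCap form using the platform's existing scheduling and alarm function, and confirmation that the consent and ethics approval cover the check. Removing the outcome costs only wording, but gives up one of the three consequences that the study set out to examine.

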### Data analysis

A descriptive analysis of all the study variables will be carried out, using the appropriate measures according to the type of variable and their corresponding 95% CIs. Firstly, depending on the groups to be compared and compliance with the application requirements, a bivariate analysis will be performed, including the chi-squared or Fisher’s exact test (qualitative variables) and Student’s t-test, ANOVA, Mann-Whitney U-test, or Kruskal-Wallis (quantitative variables), depending on the application conditions.

For the analysis of the evolution of the risk of malnutrition, McNemar’s test or Cochran’s Q test will be used for qualitative variables and paired t-test or Friedman’s rank test for quantitative variables. The incidence of risk of malnutrition and undernutrition will be calculated, as for dysphagia, during the care process and at patient discharge, estimating their corresponding Odds Ratios and 95% CI using logistic regression models.

To assess the possible risk factors for both malnutrition and dysphagia and the socio-demographic and clinical characteristics of the patients, multivariate logistic regression models will be constructed. As independent variables will include: type of nutritional care established according to the risk of malnutrition; daily intake; suspected and diagnosed dysphagia and days of stay. As control variables will include: those related to the risk profile; sociodemographic (sex, age); clinical, functional, cognitive and frailty variables. In the case of mortality and time to readmission, multivariate Cox regression models will be fitted. Independent variables will be included: level of risk of malnutrition at admission; diagnosis of malnutrition at admission; change in risk of malnutrition at admission, at 7 days and at discharge; change in nutritional status at admission, at 7 days and at discharge. Control variables will include: type of nutritional care established (according to risk of malnutrition); daily intake; contextual; related to risk profile; sociodemographic; clinical, functional, cognitive and frailty variables; suspected and diagnosed dysphagia. In all multivariate models, possible interaction effects and possible collinearity will be analyzed.

Additionally, multilevel models (generalized linear mixed models) with multivariate logistic link function will be implemented to account for possible correlation between patients admitted to the same medical or surgical units (first level) or hospital (second level).

In case of losses to follow-up, multiple imputation techniques will be used for missing data. In all cases, bilateral contrast will be used and will be considered significant when p<0.05. The analysis will be performed using SPSS v28.

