### Sample/Participants

The study population consists of the users of the medical and surgical inpatient units of the participating hospitals. Participants will be selected through consecutive case sampling.

The study will include patients aged 65 years or older who are admitted to the inpatient units, with an expected stay of at least 48h and who sign the informed consent form (or their legal guardian). Patients admitted with enteral nutrition or parenteral nutrition, terminally ill patients, patients with a primary diagnosis of cancer, patients admitted to critical care units, and with a diagnosis of COVID-19 illness at admission or during the stay will be excluded. Withdrawal criteria during follow-up will include: i) patients transferred to another hospital or unit not participating in the study; ii) any patient meeting any exclusion criteria at any time.

To calculate the sample size, the Freeman criterion for multivariate logistic regression analysis in epidemiological studies was considered first [23]. Taking into account that a maximum of 20 independent variables (k) will be included in the model at the same time and that it is intended to carry out both a global analysis and an analysis by a hospital, an initial sample size of n = 10*(k+1) = 10*(20+1) = 210 patients per hospital is estimated and, estimating possible losses of 15%, a total of 242 patients per hospital will be necessary. Secondly, given that we intend to study the prevalence of malnutrition and/or dysphagia in each of the participating hospitals and that in the literature the prevalence of malnutrition and/or dysphagia presents great variability, it seems appropriate to consider a prevalence of 50% (will guarantee the necessary sample size) which, for the confidence of 95%, a precision of 5% and a percentage of losses of 15%, will require a sample size per hospital of 453 patients (GRANMO-IMIM sample size calculator). Therefore, the total sample will be 4077 participants, and a recruitment and follow-up period of 18 months is estimated to be necessary.

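### Incidence odds ratios ignore time at risk, and adjusting for total stay does not repair them; the paired evolution tests have no place for in-hospital death and lose short stays at day 7

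*Protocol article*

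**What the plan says.** **Incidence.** The Data analysis section says that the incidence of malnutrition risk and undernutrition, and likewise of dysphagia, will be calculated over the hospital stay and at discharge, "estimating their corresponding Odds Ratios and 95% CI using logistic regression models". That sentence lists no covariates. The next paragraph describes multivariate logistic models for risk factors, and days of stay is one of their independent variables. Cox regression is reserved for mortality and time to readmission.

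**Evolution.** "McNemar’s test or Cochran’s Q test will be used for qualitative variables", with "paired t-test or Friedman’s rank test for quantitative variables".

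**Schedule.** For malnutrition risk, Variables and instruments says "All patients included in the study will be assessed on admission, every 7 days, and at discharge". For dysphagia, "Patients with a prolonged stay will be re-evaluated every 7 days". Phase 2 says "Participants will be monitored every 7 days until they are discharged from the hospital". Sample/Participants admits patients "with an expected stay of at least 48h and who sign the informed consent form", so stays well under 7 days are eligible.

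**Other relevant text.** The mixed models in Data analysis address clustering by unit and hospital, and repeated assessments within a patient are not named. Multiple imputation is planned for losses to follow-up. The Research hypothesis expects nutritional status to worsen between admission and discharge and says that this may lengthen stay and raise mortality and readmission.

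**The concern.** Both the time at risk and the number of assessments depend on how long the patient stays. A logistic model of whether the condition developed by discharge does not know how long each patient was observed. A patient in hospital twice as long has about twice the opportunity to become a case.

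The obvious repair, entering total days of stay as a covariate, works only if stay is not itself changed by the outcome. The Research hypothesis says that it may be. Total stay then includes days that came after onset and because of it, and adjusting for it conditions on a consequence of the outcome.

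The evolution tests have a related weakness. Cochran's Q and Friedman need every time point in every patient, so adding day 7 restricts the test to patients who stayed that long. No paired test has a discharge value for a patient who died, although death is the most unfavourable course. At stake are the incidence and associated-factor objectives, and part of the main objective on evolution.

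**Working it through.** The article gives no figure for this effect. The only sizing figures needed are those for sample size, and they reproduce: 1.96² × 0.5 × 0.5 / 0.05² = 384.1, rounded up to 385; 385 / 0.85 = 452.9, so 453 per hospital; 9 × 453 = 4077. After 15% losses, about 3465 remain.

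**Inputs.** The 18% incidence of malnutrition during stay is cited in the Introduction. Stay lengths, the effect of onset on stay, in-hospital mortality and incidence among the dead are assumptions, because the article does not give them.

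**1. Unequal stay, identical daily hazard.** Cumulative incidence is 1 − exp(−λ × stay). With 18% at 7 days, λ = −ln(0.82)/7 = 0.02835 per day.
- 10 days: 1 − exp(−0.2835) = 24.7%; OR = (0.247/0.753)/(0.18/0.82) = 1.49.
- 14 days: 1 − 0.82² = 32.8%; OR = (0.328/0.672)/(0.18/0.82) = 2.22.

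With reference incidence varied from 10% to 30%, the two odds ratios run over 1.46–1.55 and 2.11–2.43. The rate is the same throughout, about 2.8 per 100 patient-days at risk.

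**2. Adjusting for days of stay.** This was simulated with 400,000 patients, lognormal stay (median 7 days in the reference group, log-SD 0.6), overall incidence of 18%, and a factor with no effect on the daily hazard. Onset was observed exactly, which is kinder to every method than weekly assessment.

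| Factor multiplies stay by | Crude OR | Adjusted, stay unaffected by onset | Adjusted, onset extends remaining stay by 50% | by 100% |
|---|---|---|---|---|
| 1.25 | 1.26 | 1.03 | 0.91 | 0.82 |
| 1.5 | 1.53 | 1.07 | 0.86 | 0.72 |
| 2.0 | 2.08 | 1.17 | 0.82 | 0.62 |

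The rate ratio on time to onset stays between 0.99 and 1.01 in every row.

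A second simulation used a different stay distribution (2 days plus an exponential with mean 5 or 10 days, daily hazard 0.02). The crude OR was 1.71, significant in 100% of runs. With days of stay added it was 1.04, significant in 2%. With onset extending the remaining stay by 50–100%, the adjusted OR was 0.84–0.69, significant in 42–95%. The crude figure agrees with the closed form: 1 − exp(−0.04)/1.1 = 12.7% vs 1 − exp(−0.04)/1.2 = 19.9%, OR 1.72.

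**3. Who enters a test with a day-7 point.** With lognormal stay (log-SD 0.6), the share staying at least 7 days is 1 − Φ(ln(7/median)/0.6).
- Median 5 days: 29%, about 996 of 3465.
- Median 7 days: 50%, about 1733.
- Median 9 days: 66%, about 2295.

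This subset differs from the cohort. In the 1.5-fold simulation above, incidence was 23% among those staying 7 days or more and 18% overall.

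**4. Deaths.** If incidence is 18% in survivors, mortality is d and incidence among the dead is p, the whole cohort has (1 − d) × 0.18 + d × p. For d = 3% and p = 40% this is 18.7%. For d = 10% and p = 60% it is 22.2%.

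**The case against.** The strongest reply is that days of stay is already in the multivariate risk-factor models. A reader might infer that any factor that prolongs stay will emerge as a risk factor from the planned analysis. The article does not support that for those models: if stay is unaffected by the outcome, the covariate removes most of the bias (1.53 to 1.07, or 1.71 to 1.04). Two things remain. The incidence sentence names no covariates, and the article's own hypothesis makes stay a possible consequence of the outcome, in which case the covariate introduces bias in the other direction.

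A reader might also infer that the main evolution result describes only long-staying survivors. That goes too far. McNemar and the paired t-test compare admission with discharge, and a 3-day patient has both values. The article does not say that its main comparison has three time points; day 7 as a time point for change appears only among the Cox covariates. Short stays are lost only if Cochran's Q or Friedman is used with a day-7 point.

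Nor is death ignored by the study: in-hospital mortality is a separate outcome with its own Cox model. The gap is that the paired tests have no discharge status for patients who die. Imputation for losses to follow-up does not define one, and does not define a value for a visit that never fell due.

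The odds ratio as a measure of association is not itself a fault. The problem is the missing time at risk. Some detail may sit in a fuller analysis plan, but the methods at issue are stated here.

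**Conclusion.** The point holds in limited form. As stated, the incidence analysis is exposed whichever way stay is handled. Left out, stay alone gives an odds ratio of about 1.5 (7 vs 10 days) to 2.2 (7 vs 14 days) with no difference in rate. Included as total days, it largely corrects this if stay is independent of the outcome. Under the article's hypothesis it can push a null factor's odds ratio to about 0.7–0.9, with 0.62 as the extreme of the range tried.

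For evolution, the loss is confined to tests with a day-7 point (29–66% of patients available) and to the undefined status of those who die. All sizes rest on assumed stays, mortality and effects of onset on stay. The upward bias when stay is left out does not depend on the particular values. The downward bias after adjustment requires that onset prolongs stay.

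**What to change.** **Incidence.** Restrict to patients free of the condition at admission. Report events per 100 patient-days at risk, and cumulative incidence with death and discharge as competing events. Model onset by assessment interval using a complementary log-log link with log interval length as offset, in place of logistic regression adjusted for total days of stay. Assign onset to the interval in which it is first detected. In the closed-form example this recovers the truth: −ln(1 − 0.18)/7 and −ln(1 − 0.247)/10 both equal 0.0284, a ratio of 1.0.

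**Evolution.** Use a mixed model on all available assessments, with a patient random effect added to unit and hospital. Keep the paired admission-to-discharge change with its 95% CI. Show in-hospital death as its own category, and add a sensitivity analysis counting it as unfavourable evolution. State that status is not imputed after death or for visits that were never due.

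**Cost.** Analysis wording and more programming. No new data are needed: the 7-day assessments, days of stay and in-hospital mortality are already recorded. The drawback is that a rate or hazard ratio is less familiar to some readers than an odds ratio.
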